### Data Analyses

All statistics will be calculated using SAS Version 9.3 (SAS Institute Inc.). Baseline demographic and clinical characteristics of enrolled participants are summarized by mean and SD for continuous variables and frequency and percentage for categorical variables. A significance level of 0.05 is considered as statistically significant for all tests.

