#### Sample Size

Our goal is to obtain information critical to plan a larger trial and to understand how to use data from these trials in clinical practice. Accordingly, our sample size is based on our aims to determine feasibility and acceptability on using these devices and getting feedback from multiple stakeholders involved with their use, not on power to detect significant effects of self-monitoring on outcomes (eg, weight, HbA_1c_, and exercise). Our sample size of 60 patients is designed to provide a sufficient number of participants to obtain high retention rates, means, and variance estimates of end points that can be used to design and power the future trial. Our sample size of up to 20 clinician interviews is based upon estimates that we will likely reach data saturation within 12 or more interviews [15].

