#### Patterns of Missing Data and Attrition

The primary analytical aim of this study is to estimate individuals’ performance of all the tasks involved in the daily monitoring of weight, exercise, and glucose and responding to the SMS text message surveys for medication adherence. A proxy for this estimate will be the percentages of the 180 days of data points from the Fitbit, the wireless scale, and the glucometer that were transferred. We will calculate the percentage of 180 days on which each type of data was transferred for each participant. Patient’s respondence to SMS text message surveys to medication adherence will be calculated by the number of surveys received out of 13 time points (baseline and every other week for 6 months). To examine if the performance of all tasks differ by important clinical groups, including age (<50 vs ≥50 years), HbA_1c_ group, (<7 vs ≥7, respectively), and race (white vs black or other non-white race), we will then test whether this percentage differed by different group variable using independent samples *t* tests.

To further explore the trend in performance of all tasks (using devices for daily monitoring), we will compute proportions of missing data for each person over 2-week time periods for the entire 6-month follow up time for weight, Fitbit, and blood glucose. We will construct empirical summary plot of biweekly missingness. This consisted of plots of mean percentage missing at each biweekly period over 13 biweekly periods. At each time point, bars representing 1 SE below and above the mean are also included. To examine if the trends differ by important clinical group variables, these plots will also be produced by different age group, HbA_1c_ group, and race. We will fit a generalized linear model with this proportion as the dependent variable. Predictors included age and HbA_1c_ group, and race, with each predictor tested in separate models. Time will also be included to assess change in biweekly missingness over time, as well as interactions between time and each predictor, to assess differences in change in biweekly missingness over time by age and HbA_1c_ group and race. We will also test the change in perceived usefulness and ease of use of the devices by conducting a paired *t* test on these measures between baseline and 6-month follow-up survey.

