## Discussion

### Overview

This study provides an overview of the methodology used in a study examining the feasibility of collecting near real-time data from mHealth technologies for patients with T2DM. Determining whether it is feasible for patients to use multiple mobile devices to self-manage their diabetes is an important first step in developing effective personalized care delivery strategies.

In addition to exploring the use of mobile technology to manage chronic illness, our approach has several strengths. First the use of mixed methods to address our aims is a strength of this study. The convergence of both quantitative and qualitative elements, data collection techniques, and analyses will facilitate a more in-depth and comprehensive approach to and understanding of diabetes self-management [27]. Another strength of our study is the use of data visualizations during participant interviews as an innovative approach to enhance discussion and gain insight into the challenges and successes participants experienced in diabetes self-management with mobile devices over the past 6 months. Presenting data this way could stimulate discussion and improve communication by graphically displaying patterns and trends [28-30].

We do acknowledge several limitations to this study. The first is the limited sample size, which does not allow us to draw statistical conclusions from the data. We are not testing the effect of any intervention, so cannot assess the impact on diabetes outcomes of using these technologies. Finally, we were not able to integrate these data into the EHR to assess pragmatic aspects of the use of the data at this time within the health system.

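### Every test is judged at an unadjusted 0.05 and labelled statistically significant, although the article says the sample does not support statistical conclusions and makes estimation the primary aim

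*Protocol article*

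**What the plan says.** Three places in the protocol article bear on how the quantitative results may be read.

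- **Data Analyses** fixes the decision rule: "A significance level of 0.05 is considered as statistically significant for all tests". No test is singled out as primary.
- **Patterns of Missing Data and Attrition** opens with a different emphasis: "The primary analytical aim of this study is to estimate individuals’ performance of all the tasks". The proxy is "the percentages of the 180 days of data points from the Fitbit, the wireless scale, and the glucometer that were transferred", together with the number of medication surveys received out of 13. The section then plans:
  - independent-samples t tests of task performance by age (cut at 50 years), HbA1c (cut at 7) and race (two groups);
  - a generalized linear model for biweekly missingness of weight, Fitbit and glucose data, "with each predictor tested in separate models", with time and time-by-predictor interactions;
  - paired t tests of perceived usefulness and ease of use.
- **Discussion, Overview** names as the first limitation the "limited sample size, which does not allow us to draw statistical conclusions from the data".

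The Sample Size section justifies 60 patients by feasibility, retention, and means and variances for a later trial. It says the size is based "not on power to detect significant effects of self-monitoring on outcomes".

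**The concern.** To call a result statistically significant is to draw a statistical conclusion. The methods do this for all tests, and the discussion says the sample does not permit it. A reader cannot tell whether a group difference with P below 0.05 is to count as a result.

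This matters because the tests are many and unranked. Most of them compare patient groups that the article itself treats as clinically important, and the study is meant to inform a larger trial. A chance difference in data transmission by age, HbA1c or race could be labelled significant and carried forward. A real difference could equally be dismissed as not significant when the sample had little chance of showing it.

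**Working it through.** **No figure to reproduce.** The article gives no effect size, SD, power or number of tests, so 60 patients cannot be rederived. The checks below count the planned tests and show what the 0.05 rule implies for them.

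**Inputs from the article**
- Per-test level: 0.05 (Data Analyses). Two-sided is assumed, as sidedness is not stated.
- Patients: 60, in one cohort (Sample Size).
- Task outcomes: 3 device percentages plus the survey response, so 4. It is 3 if the t tests apply to the device percentages only, which the wording allows.
- Grouping factors: 3, each with two levels.
- Models: 3 devices × 3 predictors = 9. Each contains a group, a time and an interaction term.
- Paired t tests: at least 2.

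**Counts.** For m tests with all nulls true, the expected number of false positives is 0.05 × m. The probability of at least one under independence is 1 − 0.95^m.

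| Reading | t tests | Model terms | Paired | m | Expected | At least one |
|---|---|---|---|---|---|---|
| 4 tasks; all three terms in 9 models | 12 | 27 | 2 | 41 | 2.05 | 88% |
| 3 devices; all three terms in 9 models | 9 | 27 | 2 | 38 | 1.90 | 86% |
| 4 tasks; time counted once per device | 12 | 9 + 9 + 3 = 21 | 2 | 35 | 1.75 | 83% |
| 4 tasks; interaction only | 12 | 9 | 2 | 23 | 1.15 | 69% |
| 3 devices; interaction only | 9 | 9 | 2 | 20 | 1.00 | 64% |

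In the 35-test reading, 12 + 9 + 9 = 30 are comparisons by age, HbA1c or race. The other 5 are time effects and paired changes. For those 30 the expected number is 1.5 and 1 − 0.95^30 = 79%.

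**Allowing for correlation.** The tests share the same 60 people, and the t test on the 180-day percentage overlaps heavily with the group term for the same device. A simulation with equally correlated test statistics (100,000 draws; the correlations are assumed) gives the probability of at least one false positive:

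| m | ρ = 0.3 | ρ = 0.5 | ρ = 0.7 |
|---|---|---|---|
| 20 | 54% | 42% | 29% |
| 35 | 71% | 54% | 36% |
| 41 | 75% | 58% | 38% |

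The expected number, 0.05 × m, does not change with correlation.

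**The other direction.** Group sizes are not given, so a 30:30 split is assumed as the most favourable case. The standardised difference detectable with 80% power by the normal approximation is (1.960 + 0.842) × √(1/30 + 1/30) = 2.802 × 0.258 = 0.72 SD. The t distribution gives 0.736, about 0.74 SD. An assumed 15:45 split gives 0.84 SD by the normal approximation. At 30:30, power for an assumed true difference of 0.5 SD is 49%.

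**The case against.** The strongest reply is that a threshold for computing tests, plus a caveat on interpreting them, is common in feasibility work. The article also already leans towards caution: its primary aim is estimation, the trend models are introduced as further exploration, and the Discussion says that no intervention effect is being tested. A missing multiplicity adjustment is no finding in a condensed article on a single-cohort study.

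Much of this stands, and it rules out several stronger readings that a reader might infer:

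- **That at least 35 tests are fixed.** The text does not settle the number. 35 is one count within about 20 to 41, and not all of them are subgroup tests.
- **That chance differences will be reported as findings.** The article does not say how a P value below 0.05 will be presented, so only *could be* is supported.
- **That a false positive is 83% likely.** That figure needs independence, which overlapping outcomes in the same patients make implausible.
- **That the Sample Size section contradicts the 0.05 rule.** It disclaims power only for effects of self-monitoring on outcomes such as weight and HbA1c. The tests at issue concern data transmission and perceived usefulness. The conflict is with the Discussion and the estimation aim.
- **That subgroup P values will decide whom the later trial targets.** The article says only that retention, means and variances will be used to design and power it.

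What does not stand is that the caveat settles the matter. The rule is explicit and covers all tests, and the exploratory wording does not reach the group t tests. An unseen analysis plan could not make these two statements in the article agree.

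**Conclusion.** The point holds as an internal contradiction of minor weight. The significance rule in Data Analyses is incompatible with the limit on inference in the Discussion and sits badly with the stated aim of estimation.

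Across the readings considered, about one to two nominally significant results are expected by chance if all nulls are true. This rests on the count of tests and the 0.05 level alone. The probability of at least one, for 35 tests, is 83% under independence and about 36% to 71% at correlations of 0.7 to 0.3, which are assumed values. The detectable difference of about 0.74 SD rests on an assumed 30:30 split, and less even splits do worse. Neither a significant nor a non-significant group comparison would therefore carry the meaning that the rule gives it.

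**What to change.** Replace the significance sentence in Data Analyses with a statement along these lines: group differences, time trends and paired changes will be reported as estimates with 95% confidence intervals; these analyses are exploratory; any P values are descriptive, and no result will be declared statistically significant. Align the wording in Patterns of Missing Data and Attrition that speaks of testing whether performance differs by group, and of testing change in usefulness and ease of use. Otherwise those tests are left without a criterion.

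The cost is a few sentences and the loss of any claim of significance. The article reports that patient data are collected but their analysis is pending, so the change can be made before results are seen.

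Formal adjustment is an alternative but fits less well. Bonferroni over 35 tests gives 0.05/35 = 0.0014 per test. At an assumed 30:30 split, this raises the detectable difference from 0.72 to 1.04 SD (normal approximation) and cuts power for a 0.5 SD difference from 49% to about 10%. Holm or false-discovery-rate control would be less severe, but would still centre the report on declarations that the Discussion says the sample cannot support.

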**Figure 3 figure3:**
[figure not shown]
Example data visualizations from multiple mobile health technologies.

Using the data collected in Prompt, we will create data visualizations using 2 different data visualization software packages (Tableau and R) and pilot their use with participants via a phone interview. We will use the interviews as an iterative process to discover how to present the visualizations back to patients and to refine the visualizations. We will start with plotting the actual data transmitted from each of the devices from individuals over the entire follow-up time to show patients overall trend in blood glucose, exercise level, and weight. For blood glucose data, we will add a band of ideal blood glucose range to help patients visualize if their measurements are within targeted range. For Fitbit data, we will plot both the average active steps daily and weekly over time and also plot the steps by weekday to explore if there are any cyclic and long-term drift trends in their exercise level. For weight data, similarly, we will plot both daily weight and weekly average to show overall trend. Further details on this approach are described elsewhere [24].

#### Patterns of Missing Data and Attrition

The primary analytical aim of this study is to estimate individuals’ performance of all the tasks involved in the daily monitoring of weight, exercise, and glucose and responding to the SMS text message surveys for medication adherence. A proxy for this estimate will be the percentages of the 180 days of data points from the Fitbit, the wireless scale, and the glucometer that were transferred. We will calculate the percentage of 180 days on which each type of data was transferred for each participant. Patient’s respondence to SMS text message surveys to medication adherence will be calculated by the number of surveys received out of 13 time points (baseline and every other week for 6 months). To examine if the performance of all tasks differ by important clinical groups, including age (<50 vs ≥50 years), HbA_1c_ group, (<7 vs ≥7, respectively), and race (white vs black or other non-white race), we will then test whether this percentage differed by different group variable using independent samples *t* tests.

To further explore the trend in performance of all tasks (using devices for daily monitoring), we will compute proportions of missing data for each person over 2-week time periods for the entire 6-month follow up time for weight, Fitbit, and blood glucose. We will construct empirical summary plot of biweekly missingness. This consisted of plots of mean percentage missing at each biweekly period over 13 biweekly periods. At each time point, bars representing 1 SE below and above the mean are also included. To examine if the trends differ by important clinical group variables, these plots will also be produced by different age group, HbA_1c_ group, and race. We will fit a generalized linear model with this proportion as the dependent variable. Predictors included age and HbA_1c_ group, and race, with each predictor tested in separate models. Time will also be included to assess change in biweekly missingness over time, as well as interactions between time and each predictor, to assess differences in change in biweekly missingness over time by age and HbA_1c_ group and race. We will also test the change in perceived usefulness and ease of use of the devices by conducting a paired *t* test on these measures between baseline and 6-month follow-up survey.

We recognize that even though individuals may not provide data, they could still be compliant in weighing themselves, exercising, drawing blood glucose, and taking medication. The data may not transmit because (1) the device was not charged or (2) internet service was not available. Nevertheless, we will assess overall feasibility by examining data, which reflect both performing the measurement and being responsible for transmitting the data. Since in practice, this will be required for real-time monitoring.

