### Study Phase 2: Data Collection

Following software development, we received institutional review board (IRB) approval for phase 2. In this phase, we are conducting a mixed methods explanatory sequential designed study [14] for which we recruited 60 adults (aged ≥18 years) with T2DM. This is a 2-phase design where quantitative data are collected and followed by qualitative data collection. Patients were recruited from a primary care clinic associated with an academic medical center in the southeastern United States and through local advertisements. Eligible participants met the following inclusion criteria: (1) aged ≥18 years, (2) able to speak and read English, (3) diagnosed with T2DM, (4) told by their primary care provider to monitor their blood sugar, (5) own and use a smartphone, (6) capable of giving informed consent, and (7) able to travel for study enrollment. Participants were excluded if they had a preexisting severe medical condition(s) that would interfere with study participation (eg, renal failure, severe orthopedic conditions or joint replacement scheduled within six months, paralysis, or cancer). A proactive effort was made to enroll patients at various stages of diabetes mellitus, with treatment regimens including both oral and injectable medications were included. We purposefully targeted patients with a range of diabetes severity and included at least 25 patients with a hemoglobin A_1c_ (HbA_1c_)>7.5%. Patients were not required to have Wi-Fi or in-home internet; a smartphone with an internet connection was adequate. All other devices (eg, glucometer, cellular-enabled scale, and accelerometer) were provided to patients. Patients were excluded if they (1) had active dementia or psychiatric illness, (2) resided in a nursing home, or (3) were participating in another self-management study.

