#### Daily Monitoring

Patient weight, physical activity, and blood glucose were self-monitored via devices provided at baseline (Table 1). Patients were asked to monitor weight daily using a cellular-enabled scale by BodyTrace that connected to a cellular network. Patients were advised to weigh daily because more frequent weighing promotes better weight outcomes than less frequent weighing [19,20]. Patients also received a Fitbit Alta, a reliable and validated triaxial accelerometer for exercise monitoring [21,22]. Participants were instructed to wear the Fitbit daily. The Fitbit tracked daily number of steps taken, distance traveled, and intensity of exercise and provided feedback on these data points to patients. The devices could be worn in the shower or while swimming and were to be worn 24 hours/day and removed only to recharge the battery once per week or when indicated. The Fitbit was tethered to the Fitbit app on the participants’ smartphone via Bluetooth.

Glucose readings were tracked using a Food and Drug Administration–approved glucometer by iHealth (model BG5). Participants were instructed to monitor glucose based on the recommendations from their doctor. Like the Fitbit, the glucometer was tethered to a companion smartphone app via Bluetooth, which acted as an automatic logbook to store readings, notes, and medication dosages. Patients were given a 6-month supply of test strips for the device.

In addition to data tracking on the devices, patients received an SMS text message every 2 weeks with a link to a survey on medication adherence (over the previous week) that they completed via their smartphone. Participants clicked on the survey link, which took them to a Web-based survey in a REDCap database. We used a 3-item measure of nonadherence by Voils et al [23]. Participants were asked if over the past 7 days they (1) took all doses of my diabetes medication, (2) missed or skipped at least one dose of my diabetes medication, and (3) were not able to take all of my medication. Response options ranged from *never* (0) to always (5; Cronbach alpha=.84) [23]. Response items were scored to assess the extent of nonadherence.

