Those who failed to transmit data for a period of 7 days or longer were contacted over the phone by a research assistant to encourage reconnection with the study. If there was no response, the participant was contacted again via phone call or email 1 week later. Nonresponse at that time was considered elective withdrawal from the study. We attempted to contact any participants who withdrew to discuss their reasons for withdrawal. However, no more than 2 follow-up phone calls were made. We asked participants at baseline to please notify us of travel or other situations during which they were not able to transmit data. We made exceptions for participants who were on vacation or traveling. All mobile devices remained active until the end of the study to allow for reconnection at any point.

**Table 1 table1:** Mobile devices and data collection

Data	Instrument	Description	Data points
Exercise	Triaxial accelerometer and associated fitness app by Fitbit	Tracks data on the frequency and timing of steps	Daily: steps, minutes sedentary, minutes active, distance traveled
Weight	Cellular-enabled Scale by BodyTrace	Tracks weight	Daily weight
Glucose	Food and Drug Association–approved wireless glucometer by iHealth	Tracks blood glucose readings	As prescribed by primary care physician
Medication adherence	Self-report via short message service text message [23]	Medication adherence over the last week	Baseline, biweekly up to 6 months
Hemoglobin A_1c_	Electronic health record (EHR) laboratory results	Average level of blood sugar over the previous 3 months	Gathered from the EHR as available at baseline and 3 and 6 months post baseline

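### Glucose task performance is scored against 180 days, although each participant tests only as often as their own doctor recommends

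*Protocol article*

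**What the plan says.** The section Patterns of Missing Data and Attrition gives the primary analytical aim as estimating how well individuals perform the monitoring tasks, which it describes as daily for weight, exercise and glucose alike. It then sets the measure: "A proxy for this estimate will be the percentages of the 180 days of data points from the Fitbit, the wireless scale, and the glucometer". Transfer is counted in days, participant by participant: "We will calculate the percentage of 180 days on which each type of data was transferred for each participant". These percentages are compared by age, HbA1c (below 7 versus 7 or above) and race with independent-samples t tests. The same section computes missing-data proportions over 2-week periods for weight, Fitbit and glucose. It models them on time, one group variable at a time, and their interaction.

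The section Daily Monitoring gives participants different instructions by device. For weight: "Patients were asked to monitor weight daily using a cellular-enabled scale by BodyTrace". For activity: "Participants were instructed to wear the Fitbit daily". For glucose: "Participants were instructed to monitor glucose based on the recommendations from their doctor". Table 1 agrees: exercise and weight are listed as daily, glucose as "As prescribed by primary care physician". Eligibility (Study Phase 2: Data Collection) requires only that patients were "told by their primary care provider to monitor their blood sugar", with no minimum frequency.

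**The concern.** The denominator should count the occasions on which the task was due. For glucose, 180 days does that only for participants advised to test every day. For the others, days without a recommended test enter the score as failures, and enter the 2-week summaries as missing data. The score then mixes what was recommended with what was done, by an amount that differs between patients and is not recorded in the plan.

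Two uses of the measure are exposed. First, the Sample Size section says the 60 patients are to supply means and variance estimates for designing a larger trial; the glucose mean and variance would partly reflect recommendations. Second, the group comparisons have no term for recommended frequency, so any difference in recommendations between groups would appear as a difference in performance.

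**Working it through.** **Inputs from the protocol article.** Denominator of 180 days and 13 biweekly periods (Patterns of Missing Data and Attrition); glucose frequency set by the doctor (Daily Monitoring, Table 1); N = 60 (Sample Size); alpha 0.05 (Data Analyses; two-sided assumed). The article gives no recommended testing frequencies, so those below are assumptions.

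**The plan's own figure.** 180 / 14 = 12.86, which rounds up to 13. This matches the stated 13 biweekly periods.

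**Ceiling on the score.** A patient advised to test on d days a week, who always tests and always transmits, scores (180 × d/7) / 180 = d/7. If a 2-week period is read as 14 daily opportunities, which the text implies but does not state, the apparent missingness is 1 − d/7.

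| Recommended days/week | Days in 180 | Maximum score | Apparent 2-week missingness |
|---|---|---|---|
| 1 | 25.7 | 14.3% | 85.7% |
| 2 | 51.4 | 28.6% | 71.4% |
| 3 | 77.1 | 42.9% | 57.1% |
| 5 | 128.6 | 71.4% | 28.6% |
| 7 | 180 | 100% | 0% |

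**Ranking can reverse.** A patient advised to test daily who does so on half the days scores 50%, above the 42.9% of a perfect 3-day-a-week patient.

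**Error in the other direction.** A patient advised to test four times a day who tests once scores 100% for that day, although 1/4 = 25% of the readings were taken.

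**Effect on mean and SD.** Assume 50%, 25% and 25% of patients are advised to test 7, 3 and 1 days a week, all fully compliant. Mean = 0.50 × 100 + 0.25 × 42.9 + 0.25 × 14.3 = 64.3%, with SD 37.1 points. All of that spread comes from the recommendation.

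**Effect on the HbA1c comparison.** Each group's expected score is the sum of share × d/7. Rejection rates are from 20,000 simulated two-sided t tests at 0.05 with 30 per group. In the last column, individual compliance is drawn from the same beta(3, 1.3) distribution in both groups (mean 3/4.3 = 0.70).

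| Assumed shares at 7/3/1 days (<7 vs ≥7) | Group means, full compliance | Spurious gap | Rejection, full compliance | Rejection, equal imperfect compliance |
|---|---|---|---|---|
| 50/25/25 vs 50/25/25 | 64.3 vs 64.3 | 0 | 5% | 5% |
| 50/25/25 vs 60/20/20 | 64.3 vs 71.4 | 7.1 | 12% | 10% |
| 40/30/30 vs 60/20/20 | 57.1 vs 71.4 | 14.3 | 33% | 25% |
| 40/30/30 vs 70/20/10 | 57.1 vs 80.0 | 22.9 | about 72% | 56% |
| 30/30/40 vs 80/10/10 | 48.6 vs 85.7 | 37.1 | about 98% | 94% |

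A 20/40 split gives similar rates. With recommended days as the denominator, a fully compliant patient scores 100% at any frequency, and the test rejects in 4.8% to 5.2% of simulations under every mix when compliance is equal.

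**The case against.** The strongest defence is that the article calls the percentage a proxy and concedes its limits. That concession covers only measurements taken but not transmitted, because of an uncharged device or lack of internet. It does not mention days on which no test was due. Nor can the percentage be read as mere data density: the same section presents it as reflecting both making the measurement and transmitting it.

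A second defence is scale. This is one of four task measures in a feasibility study not sized for power, and the Discussion accepts that the sample does not support statistical conclusions. That lowers the priority, and stands to that extent. It does not excuse a descriptive estimate with the wrong denominator.

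Third, recommended frequency is not among the EHR items listed under Baseline Appointment, and about half the participants were recruited from the community. Recovery may be incomplete. That stands too, and is why a fallback is needed.

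A reader might also infer that compliant patients are classed as non-adherent. They are not: the plan sets no cut-off, so the supportable statement is that those advised to test less than daily score low.

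**Conclusion.** The glucose denominator contradicts the article's own instructions to participants and should be corrected before analysis. That part rests on the text and simple arithmetic: the score is capped at d/7 for anyone advised to test on d days a week, with d below 7, and patients advised to test several times a day can be over-credited. How many participants are affected is unknown, because no frequencies are given.

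The effect on group comparisons is conditional. A reader might conclude that the HbA1c comparison is confounded. The article shows only that a range of severity and both oral and injectable regimens were enrolled, which makes differing recommendations plausible; nothing in it links frequency to HbA1c group. Under the assumed mixes the spurious gap runs from 0 to about 37 points, and it is 0 if the mixes are equal. A gap of 57 points (100 − 42.9) would need everyone in one group to be advised daily testing and everyone in the other 3 days a week. If 80% in each group followed that pattern and 20% the reverse, the gap would be 0.6 × 57.1 = 34 points.

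The article computes each data type separately, so the weight, Fitbit and SMS results stand. This is a should-fix matter and does not threaten the study as a whole.

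**What to change.** For glucose, replace 180 with the number of test days (or readings) implied by each participant's own recommended frequency over follow-up, wherever this can be recovered from the record or the participant. Using readings also deals with the over-crediting of patients advised to test several times a day. Base the group comparisons of glucose performance on that measure.

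Where the frequency cannot be recovered, report test days per week or days out of 180 by treatment type (medications are already collected at baseline), labelled as data density and not as task performance. Keep the biweekly glucose trend, since a fall in a participant's own transmissions still informs attrition. Present it as a description of data density and attrition, and state that HbA1c-group differences in it are not to be read as differences in performance.

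The cost is a change of analysis wording and abstraction of up to 60 records, with some frequencies likely to be unrecoverable. Patient-level analysis is described as pending, so the change can still be made before results are seen. It alters only the denominator and does not touch how often anyone tests.
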